## Abstract

**Background:**

Nursing home residents with dementia are often dependent on others for mouth care, yet will react with care-resistant behavior when receiving assistance. The oral health of these elders deteriorates in the absence of daily oral hygiene, predisposing them to harmful systemic problems such as pneumonia, hyperglycemia, cardiac disease, and cerebral vascular accidents. The **purpose **of this study is to determine whether care-resistant behaviors can be reduced, and oral health improved, through the application of an intervention based on the neurobiological principles of threat perception and fear response. The intervention, called Managing Oral Hygiene Using Threat Reduction, combines best mouth care practices with a constellation of behavioral techniques that reduce threat perception and thereby prevent or de-escalate care-resistant behaviors.

**Methods/Design:**

Using a randomized repeated measures design, 80 elders with dementia from 5 different nursing homes will be randomized at the individual level to the experimental group, which will receive the intervention, or to the control group, which will receive standard mouth care from research team members who receive training in the proper methods for providing mouth care but no training in resistance recognition or prevention/mediation. Oral health assessments and care-resistant behavior measurements will be obtained during a 7-day observation period and a 21-day intervention period. Individual growth models using multilevel analysis will be used to estimate the efficacy of the intervention for reducing care-resistant behaviors in persons with dementia, and to estimate the overall efficacy of the intervention using oral health outcomes. Activity-based costing methods will be used to determine the cost of the proposed intervention.

**Discussion:**

At the conclusion of this study, the research team anticipates having a proven intervention that prevents and reduces care-resistant within the context of mouth care. Long-term objectives include testing the effect of the intervention on systemic illnesses among persons with dementia; examining the transferability of this intervention to other activities of daily living; and disseminating threat reduction interventions to nursing home staff, which may radically change the manner in which care is provided to persons with dementia.

**Trial Registration:**

ClinicalTrials.gov: NCT01363258

## Background

Older adults residing in nursing homes (NHs) experience difficulty maintaining good oral health[1-4]. Oral health in NHs has been described as "deplorable,"[[5](p251)] with evidence that "a high proportion of elderly nursing home residents suffer from poor oral hygiene and oral health neglect."[[4](p100)] The need for good oral health is significant with older adults for a variety of reasons. The majority of NH residents arrive dentate[6]. Older adults experience faster plaque production than younger adults because of the dual effects of gingival recession and reduced saliva production[7]. Poor oral hygiene causes periodontal disease which in turn creates tooth loss. The remaining teeth shift, causing loss of occlusal surfaces and subsequent chewing and swallowing problems. These problems place older adults at risk for malnutrition[8]. Other systemic diseases associated with poor oral hygiene include aspiration pneumonia, [9] diabetes, [10,11] and coronary artery disease [12-14].

The need for good oral hygiene is complicated by the dependence many NH residents have on others to provide basic care. Most require assistance in at least one activity of daily living while more than half are dependent on others for all activities of daily living, including mouth care[15]. In addition to dependence, some persons with dementia exhibit care-resistant behavior (CRB) during helping interactions. CRBs are actions "invoked by a caregiving encounter...defined as the repertoire of behaviors with which persons with dementia withstand or oppose the efforts of a caregiver."[[16](p28)]. In previous research CRBs were categorized as "uncooperative behavior,"[17-19]" "disruptive behavior," [20-22] and "agitation." [23] The progression of dementia coupled with an increased need for assistance increases the likelihood of CRB on the part of the NH resident [23,24].

Eighty percent of certified nursing assistants (CNAs) have reported experiencing CRBs while providing mouth care [25]. These behaviors ranged from mild resistance (e.g. clenching mouths closed or turning the head away) to extreme resistance (e.g., hitting or kicking the CNA) [26]. CRBs were often triggered by the CNA performing mouth care instead of allowing the older adult to do so [27]. Other precipitants to CRBs during mouth care included caregivers attempting to forcefully insert the toothbrush or swab into residents' mouths without alerting them; lack of praise or encouragement; compound commands versus simple one-step commands; no smiling or positive facial cues from the caregiver; and attempting to provide mouth care without prompts or gestures[27]. These findings support the theoretical foundation of this study, that is, CRB is a fear-evoked response to caregivers' unintentionally threatening behavior during mouth care.

As discussed in detail in another publication [28], CRB is conceptualized as behavioral responses to a perceived threat. In other words, the older adult with dementia sees the caregiving actions as a form of assault. This conceptualization of CRB is based on the neurobiology of the limbic system. The limbic system is designed to detect threat and initiate protective fear responses of freeze, flight, or fight [29-31]. The primary structure is the amygdala, comprised of varied sets of nuclei: lateral, basal, basolateral, and basomedial[29]. These nuclei interface with other structures in the limbic system, primarily the hippocampus, as well as the brainstem[32]. In a healthy brain, the hippocampus and select areas of the cerebral cortex receive and process signals from the amygdala to provide awareness, context, and judgment to the threat perception and subsequent fear response[30,33]. When the brain, especially the cerebral cortices and hippocampus, is compromised by the pathology of dementia, the ability to apply context to the perceived threat deteriorates. As reasoning and perception become altered, persons with dementia may interpret non-threatening situations (such as a CNA attempting to help the elder with mouth care) as an actual assault[33,34].

This protocol is innovative in specifically addressing threat perception and fear responses in individuals with dementia who are unlikely to have sufficient contextual or cognitive control over threat perceptions due to altered neurological structures and functions. The specific strategies proposed here are expected to reduce perceptions of mouth care and caregiver as threatening and, in turn, limit or prevent CRBs associated with automatic and reflexive fear responses.

In summary, there is a tremendous gap in knowledge regarding interventions designed to prevent and reduce CRB during mouth care in order to improve the oral health of persons with dementia. Persons with dementia and CRB have been systematically excluded from intervention studies developed to improve oral health among NH residents, even though older adults with moderate to severe dementia have worse oral health those with no or mild dementia. Interventions to address oral health outcomes for NH residents with moderate to severe dementia, and who resist care, have not been systematically examined in either nursing or dental research studies. In order to improve nursing clinical practice and to address oral health disparities, it is imperative to design studies that focus on these interventions.

The purpose of this study is to determine whether CRBs can be reduced, and oral health improved, through the application of an intervention based on the neurobiological principles of threat perception and fear response. **The primary specific aims of the study are to:**

1. Evaluate the efficacy of the Managing Oral Hygiene Using Threat Reduction (MOUTh) intervention for reducing CRBs in persons with dementia;

2. Validate the overall efficacy of the MOUTh intervention using nurse-sensitive oral health outcomes-- swollen and bleeding gums, cleanliness of the oral cavity, saliva, and integrity of the lips and oral mucosa; and

3. Calculate the cost of the MOUTh intervention.

The hypotheses based on the specific aims are as follows:

H1. Implementation of the MOUTh intervention will significantly reduce CRBs during mouth care compared to usual mouth care;

H2. The MOUTh intervention will improve oral health in older adults with dementia through the resolution of swollen and bleeding gums, improved cleanliness of the oral cavity, and the resolution of dry, cracked, and fissured oral mucosa and lips compared to usual care.

## Methods/Design

A randomized repeated measures design will be used in this clinical trial. NH residents will be randomized at the individual level to the experimental group, which will receive the intervention, or to the control group, which will receive standard mouth care from research team members who receive training in the proper methods for providing mouth care but no training in resistance recognition or resistance prevention/mediation. For baseline data collection, the behavior raters (research assistants trained to observe and record CRB) will observe both control and experimental NH residents receiving mouth care from the NH staff twice daily (AM: after breakfast but before lunch and PM: immediately after the evening meal) for 7 days. Members of the experimental and control groups will then receive mouth care from interventionists (research team members trained to provide mouth care) twice daily for 21 days, using the same schedule. A 21-day intervention period provides the greatest opportunity for obtaining the maximum benefit from the MOUTh intervention. Oral health outcome data will be collected 5 times: once prior to the 7-day observation period; once after the 7-day observation period but before the initiation of the intervention; after 7 days of intervention; after 14 days of intervention; and after 21 days of intervention. This schedule, which is depicted in Table 1 is designed to fully capture changes in oral health throughout the progression of the study.

**Table 1 T1:** Intervention & Data Collection Schedule

	Steps & Measures	Frequency
Recruitment	**Screen and Consent** Written consent from responsible party Examination of medical records to confirm inclusion/exclusion criteria Examination of NH resident for ability to hold toothbrush, raise hand to mouth MMSE Resnick et al.'s Evaluation to Sign Consent if MMSE 18 or higher Written consent from NH resident if 6/8 questions answered correctly on Resnick et al.'s Evaluation to Sign Consent	Once

Baseline, pre-observation	**Randomization (Experimental or Control) and Baseline** Baseline Chart Review (demographic data, co-morbidities) Global Deterioration Scale (GDS) Katz Activities of Daily Living (ADL) Oral Health Assessment Tool (OHAT)	Once Once Once

Days 1-7 Baseline Observations Phase	**Experimental and Control Group** Resistiveness to Care (RTC-r) OHAT Surveillance for acute infections Surveillance for psychoactive medications	Twice daily × 7 days Once, after Day 7's mouth care session Once on Day 7 for previous 7 days Once on Day 7 for previous 7 days

Intervention Phase Days 8-28	**Experimental Group** Mouth Care per MOUTh protocol RTC-r OHAT Surveillance for acute infections Surveillance for psychoactive medications **Control Group** Mouth Care per MOUTh protocol RTC-r OHAT Surveillance for acute infections Surveillance for psychoactive medications	Twice daily × 21 days Twice daily × 21 days Three times, once after Day 14's evening mouth care session, once after Day 21's evening mouth care session, and once after Day 28's evening mouth care session Three times, once on Days 14, 21, and 28 for preceding week Three times, once on Days 14, 21, and 28 for preceding week Twice daily × 21 days Twice daily × 21 days Three times, once after Day 14's evening mouth care session, once after Day 21's evening mouth care session, and once after Day 28's evening mouth care session Three times, once on Days 14, 21, and 28 for preceding week Three times, once on Days 14, 21, and 28 for preceding week

### Description of the MOUTh Intervention

The MOUTh intervention was developed and pilot-tested in a previous study[35]. It contains three components: best mouth care practices for older adults with natural dentition and dentures[36-40]; recognition of CRB[16,41]; and strategies to reduce threat perception during the provision of mouth care[35,36,40,42-44]. The mouth care protocol integrates best mouth care practices with threat reduction strategies derived from the neurobiological, nursing, and dental literature. For example, best mouth care practices included using warm water for rinsing and using interdentate brushes for flossing[36-40]. Threat reduction strategies are a constellation of techniques congruent with previously cited neurobiological and nursing studies. These techniques, which were culled from extant literature as well as from techniques that were successfully employed in a previously published pilot study[35], include interventionist behaviors designed to minimize threat appraisal, such as smiling and relaxed demeanor,[45] distraction, bridging (having an elder hold a toothbrush while the interventionist brushes the elder's teeth), and cueing (the use of polite, one-step commands)[40,42]. Interventionists are trained to encourage the elder to do as much of his or her mouth care as possible. The rationale for this technique is that self-care is unlikely to be perceived as threatening[45]. Experimental interventionists are also trained to avoid the use of "elderspeak," a term used to describe "baby talk" speech patterns associated with infants and pets but inappropriately employed when engaged with older adults: high pitch, short sentences, sing-song cadence, patronizing tone, use of collective pronouns, and infantilizing terms (baby, honey, dearie)[43,44]. Elderspeak is a documented trigger to CRB[43,44] because its dehumanizing approach heightens threat perception.

### Description of Usual Care

Usual mouth care is a challenging issue. For many persons who resist care, "usual" mouth care may mean NO mouth care[27]. Designing a study in which a potentially powerful intervention is compared to an absence of care would be meaningless. In order to have parity between the control and experimental groups, members of both will receive mouth care from interventionists from the research team. The difference will be that the control interventionists will NOT receive training in techniques designed to prevent and reduce CRB. Instead, the control interventionists will receive training separate from the experimental interventionists. That training will consist of best mouth care practices specific to older adults[36-40]. For consistency, both subjects in the control and experimental groups will receive the same mouth care supplies during the duration of the study: Biotene™ toothpaste (dentate); Biotene™ alcohol-free mouthwash (both); soft toothbrushes (dentate); denture brushes (dentures); interdentate sticks (dentate); denture cleansing paste (denture); and denture cups.

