Subjects will be recruited according to the following **inclusion criteria: **English-speaking; age 65 or older; documented diagnosis of dementia, Alzheimer's disease, vascular dementia, or Lewy body dementia; identified by NH staff as resistant to mouth care; at least 2 adjacent teeth AND/OR daily wearing of at least one denture plate; the ability to hold a toothbrush; and the ability to move his or her hand to his or her mouth. Once subjects are identified, consent will be obtained initially from the responsible party. After consent is obtained, subjects will be tested using the Mini-mental Status Examination (MMSE)[49]. Those with scores 18 or higher will be evaluated for the capacity to sign a consent form using a modification of Resnick et al.'s Evaluation to Sign Consent instrument[50]. This evaluation includes 8 questions that assess understanding of the study. Participants with dementia must score at least 6 out of the 8 questions correctly in order to sign the consent form. If the elder is deemed unable to sign the consent form assent will be obtained during each interaction between the NH resident and any member of the research team. **Exclusion criteria **are: age less than 65; no documented diagnosis of dementia; inability to hold a toothbrush; inability to raise his or her hand to his or her mouth; receiving treatment for an active dental or denture problem; or a diagnosis of dysphagia requiring thickened liquids.

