### Instruments and Measures

The schedule for data collection is listed in Table 1 located at the end of the manuscript.

***Resistance to care ***is a dependent variable for specific aim #1 and hypothesis H1 and a mediating variable for specific aim #2 and hypothesis H2. It will be measured using a refinement of the Resistiveness to Care Scale, which was developed specifically for use with persons with dementia[54]. The original instrument listed 13 behaviors. Each behavior was rated according to duration and to intensity (mild, moderate, or extreme). The original instrument was designed to be used with videotapes; thus, each behavior was recorded once and the duration for all episodes was measured using time in categories (0 = none, 1-16 seconds = 1; 17-59 seconds = 2; 1-2 minutes = 3; more than 2 minutes = 4). The original RTC was developed and tested using 68 subjects at three sites (311 observations), with α = 0.82 and Kappa values ranging from 0.82 to 0.92[54].

In our pilot study, videotaping mouth care was problematic because of confined space issues (small bathrooms) and privacy concerns[35]. As noted in the pilot study,[35] the RTC was refined and tested for this study. The refinements included removing the duration component, measuring the intensity for each individual behavior, counting the frequency of each behavior within the intensity category, summing all episodes of CRB, and then standardizing the scores by dividing the sum with the duration of mouth care (in minutes) to obtain the rate of CRBs[35].

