### Statistical Analysis

Individual growth models using multilevel analysis will be used to estimate the efficacy of the intervention for reducing CRBs in persons with dementia, and to estimate the overall efficacy of the intervention using oral health outcomes. Multilevel models (also referred to as hierarchical linear models) will be used because repeated observations of participants are nested within nursing homes[48,64-68]. Multilevel models deal with the "unit of analysis" problem that face nested studies, that is the units of analysis are not independent, but instead the observations are clustered[48,66,69,70]. Because multiple observations are nested

within participants (i.e., repeated measures), individual growth models will be used. Among the advantages of using individual growth models are the ability to deal with an unequal number of measurement occasions among individuals and heterogeneity of variance[48,65,66,71].

Three-level multilevel models will be estimated for CRBs and oral health outcomes in which the first level is the date/time at which the behaviors or outcomes are observed; the second level is the participant; and the third level is the NH in which the participant resides. Explanatory variables to be included at the first level are dosage; frequency; time; and a dummy variable for baseline versus intervention. Explanatory variables to be included at the second level are a dummy variable for whether the participant is in the intervention group or control group; functional status; cognitive impairment; demographic data (gender, ethnicity, race, age, duration of stay in a nursing home); co-morbid conditions; and the use of psychoactive medications. Variables are discussed and defined above.

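### The baseline-versus-intervention term for care-resistant behavior rests on whatever care nursing home staff gave, so it should be descriptive, with baseline delivery recorded and H1 based on the randomised contrast over Days 8-28

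*Protocol article*

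**What the plan says.** - **Baseline week (Methods/Design; Table 1).** Raters "will observe both control and experimental NH residents receiving mouth care from the NH staff twice daily". The resistiveness score is scheduled "Twice daily × 7 days", which is 14 slots per resident.
- **Intervention phase (Methods/Design).** Both arms "will then receive mouth care from interventionists (research team members trained to provide mouth care) twice daily for 21 days", which is 42 slots per resident.
- **Outcome (Instruments and Measures).** Episodes are summed and made comparable by "standardizing the scores by dividing the sum with the duration of mouth care (in minutes) to obtain the rate of CRBs".
- **Population (Recruitment, Sample, Sample Size).** Residents must be "identified by NH staff as resistant to mouth care".
- **Usual care (Description of Usual Care).** For many people who resist, usual "mouth care may mean NO mouth care". This is the stated reason for having research staff treat the control arm as well.
- **Delivery (Instruments and Measures).** The completion percentage is defined with 42 as its denominator. No counterpart is given for the 14 baseline slots.
- **Model (Statistical Analysis).** The level-1 terms include dosage, frequency, time and "a dummy variable for baseline versus intervention"; the arm dummy is at level 2. The ability to handle unequal numbers of occasions is cited as an advantage of growth models.

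**The concern.** A baseline slot without care yields no CRB rate; it does not yield zero. Every participant is selected for resistance, and the protocol itself says that care may be absent for many such people. The phase term thus compares sessions that nursing home staff gave with sessions that a research team was assigned to give.

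Two problems follow. First, the caregiver changes at the same moment as the phase, so the coefficient cannot separate the two. Second, tolerance of unequal numbers of occasions does not extend to occasions missing because of the unobserved resistance in that session.

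What is at stake is interpretation. H1 is worded against usual mouth care, but the control arm receives research-delivered care. The only staff-given usual care that is observed is the baseline week, which invites reading the phase coefficient as change from usual care.

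**Working it through.** **The plan's own figures.** Slots per resident: 2 × 7 = 14 at baseline and 2 × 21 = 42 in the intervention phase. Analysed residents: 12 × 5 = 60. Observations: 42 × 60 = 2,520, as stated. Recruitment: 60 / (1 − 0.25) = 80, as stated. The planned baseline observations, 14 × 60 = 840, are not in the power calculation, which rests on the intervention phase alone.

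**What the documents do not give.** There is no figure for the share of baseline slots with care, and nothing on how skipping relates to resistance. All inputs below are assumptions.

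**Simple illustration of session-level skipping.** Let a resident's good and bad days be equally common, at 1 and 3 CRB per minute, so the true mean is 2.0. The observed mean is (p_good × 1 + p_bad × 3) / (p_good + p_bad).

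| Care given on good / bad days | Observed baseline | Apparent rise with no true change |
|---|---|---|
| 80% / 20% | (0.8 + 0.6) / 1.0 = 1.40 | 2.0 / 1.40 − 1 = 43% |
| 80% / 40% | (0.8 + 1.2) / 1.2 = 1.67 | 2.0 / 1.67 − 1 = 20% |
| 90% / 60% | (0.9 + 1.8) / 1.5 = 1.80 | 2.0 / 1.80 − 1 = 11% |

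**Simulation of the phase coefficient.** Set-up: 60 residents, 14 baseline and 42 intervention slots, resident SD 0.7, session SD 1, about half of baseline slots delivered, all intervention slots delivered, no true effect, random-intercept model.

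| Why baseline care is absent | Phase coefficient (within-resident SD) |
|---|---|
| At random | about 0 |
| The session's own resistance (logistic slope −1) | about +0.4 |
| The resident's general resistance, or the more resistant half receiving none | about +0.01 to +0.05 |

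The third row is small because the random intercept makes the phase estimate mainly a within-resident comparison. A comparison of raw phase means would not have that protection.

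**If intervention sessions are also lost selectively.** A second set-up used resident SD 0.7, session SD 0.7, residual SD 0.3 and about 42% baseline coverage. The control-arm phase coefficient was +0.24 with no intervention sessions lost and +0.17 with 19% lost, in outcome units.

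**The randomised contrast.** With a true arm effect of −0.5 in the intervention phase, the arm-by-phase estimate in the second set-up stayed between −0.48 and −0.51 under every missingness pattern tried. An arm dummy pooled over both phases without an interaction gave about −0.40 (SE 0.18) in the first set-up, because it averages in baseline observations on which no effect can act. The Day 8-28 contrast adjusted for baseline rate and slots delivered gave about −0.50 (SE 0.07 to 0.10).

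**The case against.** The strongest reply is that the protocol's warning concerns people, not sessions. It is a general statement, qualified by its verb, that justifies the choice of control; it does not describe the baseline week in these five homes. Absence that depends only on the resident is largely absorbed by the planned multilevel model, as the simulation shows. Staff mostly discover resistance by attempting care, and with a rater present an attempt that meets resistance would be scored. Staff under observation may give care at every slot, and skipping may follow workload. This stands: a reader might infer that the phase term is biased by construction, or that baseline covers only easy days, and the documents support neither.

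A reader might also infer that selected baseline sessions are set against every scheduled intervention session. That is too strong. Completion is counted out of 42, and assent is sought at each interaction for residents who cannot sign consent, so intervention sessions can be lost too.

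The direction is likewise open. The Background lists caregiver behaviors that provoke resistance, so untrained staff could raise the baseline rate.

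Finally, H1 is tested against a concurrent control arm, the article makes no pre/post efficacy claim, and handling of empty slots may be in an analysis plan that is not shown. This limits the point to secondary quantities. It does not remove it: the article itself puts the phase dummy in the CRB model and itself defines delivery only for the phase in which the research team gives the care.

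**Conclusion.** The concern holds in limited form. The phase coefficient and within-arm change are not clean measures of change from usual care, because the caregiver switches with the phase whatever the coverage. Selection bias comes on top only if staff skip a resident's more resistant sessions: about +0.4 within-resident SD at an assumed 50% coverage, and close to zero if absence is random or purely resident-level. Which case applies cannot be told from the documents, and as described the data would not show it.

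It would be wrong to conclude that the trial's main result is biased. Randomisation is individual and the baseline procedure is the same in both arms, so the selection does not bias the arm contrast. The cost there is precision, through a thinner baseline. The change is worth making but does not threaten the design.

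**What to change.** 1. Have the raters code each of the 14 baseline slots as care delivered or not delivered.
2. Base H1 on the randomised arm contrast over Days 8-28, the 42 observations per participant already used for power. Adjust for each resident's mean baseline CRB rate, with a missing indicator for residents who have none, and for the number of baseline slots delivered.
3. State that the baseline-versus-intervention coefficient and within-arm change are descriptive and are not evidence that CRB rose or fell from usual care.

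The cost is one field per baseline slot, at times when raters are already scheduled to observe, plus a few sentences of analysis text. The field should be in place before data collection, since it may not be recoverable reliably afterwards. The small downside is giving up pre/post claims.
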